### Data collection and data management

Data will be collected through case report forms at each of patients’ visit. A study database will be generated to enter data using EpiData software version 3.1. All the informed consent and case report forms will be locked in the research closet with the access to researchers only at Guang’anmen Hospital, China Academy of Chinese Medical Sciences. All data will be double checked and merged at the end and delivered to the statisticians for analysis. Regarding the quality control, all heat-stone massage providers and outcome assessors at each site will be trained about the standard operation procedure before the start of this trial. The training will include diagnosis of chronic musculoskeletal pain, inclusion and exclusion criteria, operation of the heat-stone, location of the massage points, massage manipulation techniques, the use of the tools for the outcome assessments, and the completion of case report forms. The trial will be monitored by the clinical research center of China Academy of Chinese Medicine.

### Power analysis and sample size calculation

The power analysis and sample size estimation were based on the primary outcome of this trial which is the change in GPS from baseline to the end of the 2 week intervention. One of our pilot studies showed that the mean change in GPS in heat-stone group was 12, while the mean change in GPS in flurbiprofen was 8, with a combined standard deviation of 6.7. With a power of 80%, 2-sided alpha of 0.05, and the assumption that the change is normally distributed, we used the “power twomeans” function in STATA with 1:1 ratio in treatment and control group to get estimated sample size of 46 samples for each group, so that a total of 92 participants are required. Considering the 20% dropout rate, the total sample size of 115 is required. To make it convenient to assign the participants with 2:1:1 ratio to the 3 centers, we took the 120 as the final planned sample size. The sample size was calculated using STATA, version 16.1 (StataCorp, USA).

### Statistical analysis

The Primary analysis will be conducted on the full dataset of all the participants after randomization based on the intention-to-treat principle. Moreover, sensitivity analysis will be conducted between the full dataset and the per protocol dataset. Participants who are not in the per protocol analysis are nonadherence which might be caused by failure to receive the assigned treatment, suffering from severe adverse events, or loss of follow-up.

To check if there is selection bias and confounding factors, we will compare the baseline characteristics of the two groups. Continuous variables will be described as mean (Standard Deviation) for normal distribution and be tested using t test or be described as median (interquartile range) for skewed distribution and be tested using Mann–Whitney test. Categorical variables will be summarized as counts (percentages) and be tested using Chi squared test or Fisher exact test.

The primary outcome of this trial is the change in Global Pain Scale from baseline to the end of the 2 week intervention. The difference of the changes between the two groups will be analyzed using a generalized linear mixed model. The mean and 95% confidence interval will be calculated and estimated. Known confounding factors that may affect the pain severity in chronic musculoskeletal patients include age, sex, job, duration of the chronic pain, and emotional state. Therefore, we will make the subgroup analysis for the variables of age categories (>60 years vs. ≤60 years), sex (female vs. male), job categories, duration of pain, taking these as covariates in the model.

For the secondary outcomes, generalized linear mixed model will be used for continuous variables, and two proportion z test will be used for proportions, whereas the Chi squared test or Fisher exact test will be used for categorical variables.

The primary economic analysis will be the cost-utility analysis over 6 week using quality-adjusted life years (QALYs) calculated from the SF-36. The mixed-effect linear regression model will be used, adjusting the confounding factors including age, sex, job, and site of recruitment.

All statistical tests will use the statistical significance of 2-sided *p* value of <0.05. All the statistical analysis will be performed using Python, version 3.8.16 (sklearn and statsmodels packages).

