### Safety and adverse event reporting

We will monitor the adverse events through the trial, that will be achieved by a research board composed by 1 physician, 1 nurse, and 1 statistician. Because the intervention contains heat therapy and pressure on the skin, empyrosis, bruise, and over sweating are likely to occur during the treatment. Any adverse events related to the study intervention will be reported.

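### The one stated sensitivity analysis compares the full set with a per-protocol set defined by post-randomization events, so it cannot test robustness to the planned 20% dropout

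*Protocol article*

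**What the plan says.** The Statistical analysis section of the protocol article makes the intention-to-treat analysis primary: "The Primary analysis will be conducted on the full dataset of all the participants after randomization based on the intention-to-treat principle". On the model it says: "The difference of the changes between the two groups will be analyzed using a generalized linear mixed model". The one robustness check it states is that "sensitivity analysis will be conducted between the full dataset and the per protocol dataset". Participants outside the per-protocol set are described as "nonadherence which might be caused by failure to receive the assigned treatment, suffering from severe adverse events, or loss of follow-up".

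Three other places bear on this:

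- Safety and adverse event reporting ties the expected events to the heat and pressure of the intervention: "empyrosis, bruise, and over sweating are likely to occur during the treatment". It names no event for the plaster.
- Power analysis and sample size calculation plans for loss: "Considering the 20% dropout rate, the total sample size of 115 is required".
- Randomization and blinding says that participants and massage therapists know the treatment. Outcome assessors and the analysing statistician are blinded.

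**The concern.** A sensitivity analysis should change an assumption on which the primary result rests and show whether the conclusion survives. With a fifth of patients expected to be lost, the assumption most in need of testing is that the missing patients would have done as the observed data predict. The per-protocol comparison does not change it. It leaves out the same unobserved patients and then removes some observed ones as well.

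The grounds for removal are a second problem. Not receiving treatment, having a severe adverse event and being lost to follow-up can all depend on the assigned arm and on how the patient is doing. Patients know their arm, and GPS is a symptom score. What remains in each arm is therefore no longer a randomized comparison. A severe adverse event is also a result of treatment. A patient who attended every session and had such an event adhered in full.

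The risk is that readers take agreement between the two analyses as evidence of robustness, when on dropout it carries no such information.

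**Working it through.** **Inputs.** From Power analysis and sample size calculation: "the mean change in GPS in heat-stone group was 12, while the mean change in GPS in flurbiprofen was 8", SD 6.7, power 80%, two-sided alpha 0.05, dropout 20%, final total 120 (60 per arm). The outcomes of excluded or missing patients are not in the document. They are assumptions here and are varied.

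**Step 1: the plan's own figures.** A two-sample t-test with difference 4 and SD 6.7 needs n = 45.02, rounded up to 46 per arm, or 92 in total. Then 92 / (1 − 0.20) = 115. The stated figures reproduce and are not in dispute.

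**Step 2: direction of the per-protocol bias.** Let patients kept in the set improve by 12 (massage) and 8 (plaster), so the per-protocol difference is 4.0. Let p_M and p_C be the fractions left out, and m_M and m_C their true mean improvements. The difference in all randomized patients is

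(1 − p_M)·12 + p_M·m_M − [(1 − p_C)·8 + p_C·m_C].

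| Left out, massage / plaster | Their mean improvement, massage / plaster | All randomized | Per-protocol minus all randomized |
|---|---|---|---|
| 20% / 20% | 12 / 8 | 4.0 | 0 |
| 20% / 20% | 0 / 0 | 3.2 | +0.8 |
| 20% / 20% | 0 / 8 | 1.6 | +2.4 |
| 20% / 20% | 8 / 0 | 4.8 | −0.8 |
| 25% / 15% | 0 / 0 | 2.2 | +1.8 |
| 15% / 25% | 0 / 0 | 4.2 | −0.2 |
| 10% / 30% | 0 / 0 | 5.2 | −1.2 |

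For example, the third row is 0.8 × 12 + 0.2 × 0 − 8 = 1.6. More extreme pairings widen the range: 30% / 10% with 0 / 8 gives 0.4 (+3.6), and 10% / 30% with 8 / 0 gives 6.0 (−2.0). The sign is not fixed.

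**Step 3: what the planned comparison can see.** Two kinds of exclusion must be kept apart.

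- *Excluded but observed* (for example, a severe event with week-2 GPS recorded). The full set contains these outcomes. If 3 of 60 massage patients are excluded with no improvement, the full-set difference is 57 × 12 / 60 − 8 = 3.4, against 4.0 per protocol. If 6 of 60, it is 54 × 12 / 60 − 8 = 2.8, against 4.0. The gap is visible.
- *Lost to follow-up.* Week-2 outcomes are in neither analysis. Both estimates rest on observed data, so they can agree however badly the missing patients did.

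**Step 4: how much the missing patients could matter.** Take 48 observed per arm (20% of 60 missing), an observed difference of 4.0, and shift only the missing massage patients down by d points. The standard error is held fixed.

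- SE = 6.7 × √(2/48) = 1.37.
- Difference in all randomized = 4 − 0.2d.
- Significance is lost when 4 − 0.2d < 1.96 × 1.3676 = 2.68, so d > 1.32 / 0.2 = 6.6.

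Missing massage patients would then improve by about 12 − 6.6 = 5.4 instead of 12. If they did only as well as plaster (d = 4), the difference is 3.2 and z = 3.2 / 1.37 = 2.34, still significant.

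If only 10% were missing at week 2 (54 observed per arm), SE = 6.7 × √(2/54) = 1.29 and d = (4 − 1.96 × 1.2894) / 0.1 = 1.473 / 0.1 = 14.7. That would mean worsening from baseline. The result is therefore sensitive to the loss rate, which is a reason to run the analysis on the actual data.

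**The case against.** The strongest reply has five parts.

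1. *The wording may list causes, not criteria.* The sentence says nonadherence might be caused by a severe adverse event, so a patient with an event who kept to treatment might stay in the set. This reading is available. It leaves the text needing clarification, and it does not touch loss to follow-up, which takes patients out on either reading.

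2. *The direction of bias is not established.* This stands. A reader might infer that the per-protocol set is bound to favour massage. The article does not support that. It calls the expected events likely but not severe, gives no exclusions by arm, and does not say that plaster patients will have none. Step 2 shows the sign reversing.

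3. *Harm-related exclusions would be exposed, not hidden.* This also stands where week-2 GPS is recorded: 3.4 or 2.8 against 4.0 is a visible gap, with the primary analysis the less favourable. The false reassurance concerns unobserved patients only.

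4. *A condensed article may leave missing-data analyses to a statistical analysis plan that is not shown, and it never says this comparison tests missing data.* That is so, and the absence of further analyses is not the point. The point is that the one sensitivity analysis the article fixes is poorly suited to the main threat to the primary result. The 20% is also not tied to day 14. Follow-up runs to day 42, so week-2 loss may be smaller.

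5. *A set defined by sessions attended would still lose patients who stopped because of harm.* True. No per-protocol definition restores randomization, which is why the analysis should be supplementary however it is defined.

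**Conclusion.** The concern holds in a limited form. The per-protocol set rests on post-randomization events and can be biased either way. The listed scenarios run from +2.4 to −1.2 points on a 4-point effect, and more extreme assumptions run from +3.6 to −2.0. Bias toward massage is plausible through its heat and pressure harms but is not a certainty.

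The firmer part is that agreement between the two analyses says nothing about patients lost to follow-up. The 6.6-point tipping value shows that this could decide the result. It assumes 20% missing in each arm at week 2, completers at the planning means, a shift in massage only, and a fixed standard error.

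A reader might infer that the primary result itself is compromised. It is not: the primary analysis stays intention-to-treat, and the sample size reproduces. The severity is moderate.

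**What to change.** - Make the sensitivity analysis of the primary outcome a multiple imputation of week-2 GPS in all randomized patients. Use either a delta adjustment varied by arm up to the tipping point, or control-based imputation. The imputation model should include arm, centre, baseline GPS and week-1 GPS. Table 1 already schedules GPS at baseline, day 7 and day 14.
- Label the per-protocol analysis supplementary. Define it by treatment actually received (sessions attended, plaster use), and fix the membership rules before the analysing statistician is unblinded.
- State that a severe adverse event alone does not remove a patient from the per-protocol set.

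The cost is a change of wording and one standard extra analysis, with no new data. The robustness result may look less favourable than the planned comparison would. The primary analysis does not change.

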### Baseline assessment

Baseline visit and assessment will be conducted at the inpatient centers in the hospitals. Demographic information (including sex, age, educational background, job), course of the chronic pain, medical history (including complications, smoking, alcohol), and basic tests (including blood pressure, heart rate), will be collected in person. Baseline assessment about the chronic musculoskeletal pain will include severity of the pain (assessed by Numerical Rating Scale, range 0–10, higher scores indicate worse pain), pain-related overall life assessment (measured by Global Pain Scale, range 0–200, higher scores indicate worse influence on life), acceptance of pain (assessed by Chronic Pain Acceptance Questionnaire, range 0–120, higher scores indicate higher pain acceptance), health education and self-management (assessed by the Health Education Impact Questionnaire, range 40–200, higher scores indicate better health self-management), pain-related self-efficacy (assessed by the Pain Self-Efficacy Questionnaire, range 0–60, higher scores indicate better confidence of self-efficacy), anxiety and depression (assessed by the Hospital Anxiety and Depression Scale, range 0–42, higher scores indicate more severe symptoms), and quality of life (assessed by Short Form-36, range 0–100, higher scores indicate better health). All scheduled visits are shown in the Table 1.

**Table 1 tab1:** The schedule of planned visits.

Study component	Visit 1	Visit 2	Visit 3	Visit 4	Visit 5	Visit 6	Visit 7	Visit 8
Time	1 d before treatment	First treatment	7 ± 1 d after treatment	14 ± 1 d after treatment	21 ± 1 d after treatment	28 ± 1 d after treatment	35 ± 1 d after treatment	42 ± 1 d after treatment
Informed consent	×	–	–	–	–	–	–	–
Demographic	×	–	–	–	–	–	–	–
Pain duration	×	–	–	–	–	–	–	–
Pain locations	×	–	–	–	–	–	–	–
Pain triggers	×	–	–	–	–	–	–	–
Randomization	×	–	–	–	–	–	–	–
Intervention	–	×	×	×	–	–	–	–
NRS	×	–	×	×	–	–	–	×
GPS	×	–	×	×	–	–	–	×
CPAQ	×	–	×	×	–	–	–	×
heiQ	×	–	×	×	–	–	–	×
PSEQ	×	–	×	×	–	–	–	×
HADS	×	–	×	×	–	–	–	×
SF-36	×	–	×	×	–	–	–	×
Pain killer intake	×	–	×	×	–	–	–	×
Adverse events	–	×	×	×	×	×	×	×

NRS, Numerical rating scale; GPS, Global pain scale; CPAQ, Chronic pain acceptance questionnaire; heiQ, Health Education Impact Questionnaire; PSEQ, Pain Self-Efficacy Questionnaire; HADS, Hospital anxiety and depression scale; SF-36, Short Form-36.

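### Baseline significance tests are planned as a check for selection bias and confounding, a job they cannot do; the harm is to interpretation, not to the primary estimate

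*Protocol article*

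**What the plan says.** The Statistical analysis section of the protocol article gives the baseline comparison an inferential purpose: "To check if there is selection bias and confounding factors, we will compare the baseline characteristics of the two groups". Continuous variables are to be summarised by mean and SD and "be tested using t test or be described as median (interquartile range) for skewed distribution and be tested using Mann–Whitney test". For the rest, "Categorical variables will be summarized as counts (percentages) and be tested using Chi squared test or Fisher exact test". The level is set once for everything: "All statistical tests will use the statistical significance of 2-sided" p below 0.05.

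The article does not say which baseline characteristics will be tested. Its Baseline assessment section lists what is collected: "Demographic information (including sex, age, educational background, job), course of the chronic pain, medical history (including complications, smoking, alcohol), and basic tests"; the basic tests are blood pressure and heart rate. Seven scales follow (NRS, GPS, CPAQ, heiQ, PSEQ, HADS, SF-36). Table 1 adds further Visit 1 items such as "Pain locations" and pain triggers.

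Three other statements bear on the point.

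- Randomization and blinding describes 1:1 allocation from a central system, in blocks of 6, with a separate list for each of three centres.
- The Discussion credits randomisation with controlling measured and unmeasured confounders.
- Statistical analysis names age, sex, job, pain duration and emotional state as known confounders. The variables it then takes into the model as covariates are age, sex, job and pain duration; emotional state is not among them.

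**The concern.** A test of a baseline variable between randomised arms has a null hypothesis that is true by design, provided allocation was carried out as planned. A small p-value then says only that a rare draw occurred; it is not evidence of selection bias. A large p-value is no reassurance, because the test measures whether a difference is surprising, while confounding depends on the size of the difference and on how strongly the variable predicts outcome.

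At stake is how the trial is read. A well-run trial could report apparent selection bias because one variable crossed 0.05. Conversely, a moderate imbalance in a prognostic variable could be dismissed because it did not.

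**Working it through.** **Inputs**

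- Sample size 120, 1:1, so 60 per arm. (The article's own calculation reproduces: difference 12 − 8 = 4, SD 6.7, 80% power and two-sided 0.05 give 45.02 per group by the t-based method, rounded up to 46; 92 / 0.8 = 115, raised to 120.)
- Level 0.05 per test.
- Number of variables, counted from Baseline assessment: sex, age, education, job, course of pain, complications, smoking and alcohol (8), blood pressure and heart rate (2), seven scale totals (7), together 17. Two blood pressure values make 18; pain locations and triggers make 20. The article states no figure for the baseline tests that could be reproduced.

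**False flags, independent tests.** P(at least one p < 0.05) = 1 − 0.95^k.

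- k = 17: 58.2%
- k = 18: 60.3%
- k = 20: 64.2%
- The expected number of flags is 17 × 0.05 = 0.85 to 20 × 0.05 = 1.0. The 50% mark is passed at k = 14 (51.2%; k = 13 gives 48.7%). With only 10 variables tested the chance is 40.1%.

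**False flags, correlated tests.** The correlations are assumptions. Simulation of correlated normal test statistics, 200,000 runs per case:

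| Assumed correlation | k = 17 | k = 18 | k = 20 |
|---|---|---|---|
| Scales 0.3–0.5, others 0–0.1 | 53–56% | 56–59% | 60–63% |
| Scales 0.7, others 0.3 | 47% | 49% | 52% |
| All variables 0.3 | 49% | 51% | 54% |
| All variables 0.5 | 39% | 40% | 42% |

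**Effect of the test used.** For a binary variable with 60 per arm, the true size of the Fisher test is 2.2% to 3.5% (prevalence 10% to 50%), while chi-squared stays near 5%. As an illustration, suppose 6 of 17 independent tests were Fisher tests of that size. The chance is then 1 − 0.95^11 × 0.978^6 = 50% up to 1 − 0.95^11 × 0.965^6 = 54%. Fisher tests combined with strong correlation would lower it further; that combination was not calculated.

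**False reassurance.** The smallest observed difference that reaches significance is 1.96 × √(2/60) = 0.36 SD. To see what may pass, take an observed imbalance of 0.35 SD in a covariate that correlates 0.3 to 0.5 with GPS change (assumed). With SD 6.7, the unadjusted arm difference shifts by 0.35 × 0.3 × 6.7 = 0.7 to 0.35 × 0.5 × 6.7 = 1.2 points, which is 18% to 29% of the 4-point difference used for sample size.

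**Ability to detect subverted allocation.** If tampering made the arms truly differ by 0.3 SD on a variable, the test of that variable would be significant 38% of the time; for 0.2 SD, 19%. These chances have to be read against about one chance flag expected across the whole table.

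**The case against.** The strongest reply is that nothing depends on these p-values. The article states no action, covariate selection or change of conclusion after a significant baseline test, and its covariates are named independently of the tests. This stands. A reader might infer a decision rule that can distort the primary result; the text contains none, and the primary estimate, its interval and its type I error are unaffected.

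A reader might also infer that a false alarm is more likely than not. That needs all 17 or more variables to be tested and to be no more than moderately correlated. The article says only that baseline characteristics are compared, and seven of the listed items are pain-related or psychosocial scales that probably move together. Strong correlation takes the chance below one half, so only a range is defensible.

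Finally, a reader might infer that the tests are wholly uninformative about selection bias. That is too absolute. Whether allocation was subverted is the very question of a selection-bias check, and fixed blocks of 6 with unblinded participants and therapists make the question a fair one. Subversion would make the null false and could move the tests. But the power is low and a flag cannot be told from chance. Nothing in the article suggests that allocation was or will be subverted.

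The descriptive summaries by arm are already planned, so that part of the remedy is not new.

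**Conclusion.** The point holds in limited form. The article assigns baseline significance tests a purpose they cannot serve: under properly conducted randomisation a significant result is chance, and a non-significant result leaves observed differences up to about 0.36 SD unflagged. The chance of at least one false flag is roughly 40% to 64% if all 17 to 20 listed variables are tested; it rests on the assumed correlation and choice of test, and is lower if fewer variables are tested. For confounding the check is invalid; for selection bias it is weak and ambiguous. The consequence is confined to interpretation, so this is a minor point, worth making because the correction is nearly free and because emotional state, named as a confounder, is left out of the covariates.

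**What to change.** Delete the baseline tests and the sentence that gives them their purpose. Keep the summaries by arm that are already planned (mean and SD, median and interquartile range, counts and percentages), with standardised differences if wanted. Control imbalance through covariates fixed in advance, whatever differences are observed: age, sex, job and pain duration as now, plus baseline GPS and baseline HADS. Possible wording:

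> Baseline characteristics will be summarised by arm without significance tests. The primary model will include baseline GPS, baseline HADS, age, sex, job and pain duration as covariates, irrespective of observed baseline differences.

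The cost is a sentence or two and less analysis. GPS and HADS are already measured at Visit 1, so no data collection, sample size or patient procedure changes. To the extent that the two scores predict the outcome, adjusting for them gains precision and removes the effect of chance imbalance in them. If the full protocol or analysis plan already fixes these covariates, only the deletion remains.

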### Study outcomes and assessment

The primary outcome is the change in the score of Global Pain Scale (GPS, range 0–200, higher scores indicate worse influence on life) from baseline to the end of the 2 week intervention. The GPS is a validated, concise, and easily interpreted score to comprehensively assess the pain, emotions, clinical outcomes, and daily activities (11). The Chinese version of the GPS was also validated in Chinese population (12).

The secondary outcomes include (1) the change in GPS from baseline to the end of 6 week follow-up; (2) the proportion of participants who have clinically significant change in severity of the pain assessed by Numerical Rating Scale (NRS, range 0–10, higher scores indicate worse pain) (13), a change of 20% from baseline to the end of the 2 week intervention is regarded as clinically significant change (14); (3) the change in acceptance of pain assessed by Chronic Pain Acceptance Questionnaire(CPAQ, range 0–120, higher scores indicate higher pain acceptance) from baseline to the end of 2 week intervention (15); (4) the change in health education and self-management assessed by the Health Education Impact Questionnaire (heiQ, range 40–200, higher scores indicate better health self-management) from baseline to the end of 2 week intervention (16); (5) the change in pain-related self-efficacy assessed by the Pain Self-Efficacy Questionnaire (PSEQ, range 0–60, higher scores indicate better confidence of self-efficacy) from baseline to the end of 2 week intervention (17); (6) the change of anxiety and depression assessed by the Hospital Anxiety and Depression Scale (HADS, range 0–42, higher scores indicate more severe symptoms) from baseline to the end of 2 week intervention (18); (7) the change in quality of life assessed by Short Form-36 (SF-36, range 0–100, higher scores indicate better health) from baseline to the end of the 2 week intervention (19).

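### Emotional state is named among five factors that may affect pain but is the only one not carried into the covariate list, and the plan leaves unclear whether any of the five is in the primary GPS model

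*Protocol article*

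**What the plan says.** All of the relevant analysis text is in the Statistical analysis section of the protocol article.

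- For the primary outcome, the change in GPS to the end of the 2-week intervention: "The difference of the changes between the two groups will be analyzed using a generalized linear mixed model". That sentence names no covariates.
- The known factors that may influence pain severity are then said to "include age, sex, job, duration of the chronic pain, and emotional state".
- The following sentence draws a consequence from that list: "Therefore, we will make the subgroup analysis for the variables of age categories". It goes on to "sex (female vs. male), job categories, duration of pain, taking these as covariates in the model". Emotional state does not appear.
- The only other covariate list in the section belongs to the economic model (age, sex, job and recruitment site). It does not include emotional state either.

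A baseline measure of emotional state is planned. The Baseline assessment section includes "anxiety and depression (assessed by the Hospital Anxiety and Depression Scale", and Table 1 schedules HADS at Visit 1, the day before treatment. Under Study outcomes and assessment, GPS is described as a tool to "comprehensively assess the pain, emotions, clinical outcomes, and daily activities", and change in HADS is a secondary outcome.

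**The concern.** The covariate sentence is presented as following from the list of five factors, yet it uses four. Nothing explains why emotional state is treated differently, and the measure for it is already collected.

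Two things are at stake.

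- **Precision.** A baseline variable that predicts GPS change, left out of the model, leaves its share of the variance in the residual.
- **Chance imbalance.** The Randomization and blinding section describes separate lists for the three centres with blocks of 6 and no balancing on emotional state. The arms may therefore differ on it by chance. If the planned baseline comparison shows such a difference, readers can point to the protocol's own list of factors. An adjustment added at that stage would look post hoc.

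The wording creates a second problem. Because subgroup analysis and covariate adjustment share one sentence, an analyst cannot tell whether the four named variables belong in the primary GPS model or only in the subgroup models.

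**Working it through.** **1. Listed factors against carried factors**

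| Factor named as affecting pain | Carried into the subgroup/covariate sentence |
|---|---|
| Age | Yes (above 60 or not) |
| Sex | Yes |
| Job | Yes |
| Duration of pain | Yes |
| Emotional state | No |

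**2. The plan's own sample size**

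Inputs from the Power analysis and sample size calculation section: mean changes of 12 and 8, so a difference of 4; SD 6.7; power 80%; two-sided alpha 0.05; dropout 20%; final total 120.

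- The two-sample t calculation (noncentral t) gives 46 per group, with power 80.9%. This agrees with the stated 46 per group and 92 in total.
- 92 / (1 − 0.20) = 115, as stated.
- Completers expected from 120: 120 × 0.80 / 2 = 48 per arm. Power is then 82.5%.

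The sample size is not in dispute.

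**3. What adding baseline HADS would change**

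Assumption: r is the within-arm correlation of Visit 1 HADS with GPS change, given any other covariates in the model. The document does not give it, so a range of 0.1 to 0.4 is shown.

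- Residual SD = 6.7 × √(1 − r²)
- Standard error of the difference = residual SD × √(2/48), where √(2/48) = 0.204
- 95% half-width = 1.96 × standard error
- Power from the noncentral t at 48 per arm, difference 4

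| r | Residual SD | Standard error | Half-width | Interval narrower by | Power |
|---|---|---|---|---|---|
| 0 | 6.70 | 1.37 | 2.68 | – | 82.5% |
| 0.1 | 6.67 | 1.36 | 2.67 | 0.5% | 82.9% |
| 0.2 | 6.56 | 1.34 | 2.63 | 2.0% | 84.0% |
| 0.3 | 6.39 | 1.30 | 2.56 | 4.6% | 85.9% |
| 0.4 | 6.14 | 1.25 | 2.46 | 8.3% | 88.5% |

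**4. Effect of a chance imbalance**

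A one-standard-error imbalance in baseline HADS is 0.204 SD at 48 per arm. It moves the unadjusted estimate by r × 6.7 × 0.204. At r = 0.3 this is 0.41 GPS points, about 10% of the planned difference of 4. Against the unadjusted standard error of 1.37 it is 0.41 / 1.37 = 0.3 of a standard error, which is the fairer yardstick.

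**The case against.** The strongest reply is that the omission is from a subgroup sentence, not clearly from the primary model. The sentence that defines the primary analysis names no covariates, and the Discussion presents the prespecified subgroup analysis as a way to find interactions. On that reading the primary comparison adjusts for none of the five factors, and dropping emotional state from the list does not by itself cost precision there. This stands. It limits the claim, and it also shows that the wording needs repair.

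The gain may also be small. At r of 0.1 to 0.2 power rises by at most 1.5 percentage points, from a start already above 80%. GPS includes emotions, so a change score, or a baseline GPS term if one were added, may already absorb part of what HADS carries. Excluding patients with a history of mental disorders may narrow the range of HADS. These points stand as well.

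A reason for the omission can be imagined: HADS is itself a secondary outcome. But that argues only against using a later value, not the Visit 1 value, and the plan does not offer it.

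Three stronger readings are tempting, and the document supports none of them.

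- **That the primary estimate is biased.** Treatment is randomised, so the unadjusted estimate is unbiased, and its interval already allows for chance imbalance.
- **That the plan omits the factor that drives the primary outcome or is tied most closely to it.** The text says only that the factors may affect pain severity. It does not rank them, and a factor linked to pain level need not predict two-week change in GPS.
- **That the other four factors are certainly in the primary model.** The sentence does not settle this.

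**Conclusion.** The inconsistency is real. Five factors are listed, four are carried forward, and the one left out has a baseline measure scheduled for every patient. This goes beyond detail left to a statistical analysis plan, because the protocol states a specific list that does not follow from the sentence it rests on.

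The consequence is modest: some precision forgone and chance imbalance left uncorrected, with neither systematic bias nor an underpowered trial on the plan's own inputs. The power and interval figures rest on the planned difference of 4, the SD of 6.7, 48 completers per arm and an assumed r. If baseline GPS is also adjusted for, the relevant r may lie at the low end of the range or below it. The inconsistency holds whatever r is. The case for acting is that the change is nearly free and removes an ambiguity about the primary model.

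**What to change.** In the Statistical analysis section, and before unblinded data are examined:

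1. State that the primary GPS model includes the listed baseline factors as covariates.
2. Add the Visit 1 HADS score to that model as a continuous covariate. Specify the Visit 1 value, because HADS measured after treatment starts is an outcome. If the sponsor prefers to leave emotional state out, give the reason.
3. Describe the subgroup analyses in a separate sentence, as treatment-by-subgroup interactions, so that they are not confused with covariate adjustment.

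The inconsistency shown here does not by itself call for extending the covariate to the secondary-outcome models, for which the plan names no covariates.

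Cost: a few lines of text, no new data and one degree of freedom. The gain may be slight if baseline GPS is also in the model.
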